## Abstract

**Background:**

Long-term recurrent weight gain remains a persistent challenge in metabolic bariatric surgery (MBS). One strategy for managing recurrent weight gain involves the placement of a non-adjustable silicone ring around the reduced stomach pouch. This technique may lead to more significant weight loss and a reduced risk of long-term recurrent weight gain. Although several studies have demonstrated the effectiveness of silicone rings in combination with Roux-en-Y gastric bypass (RYGB), randomized studies providing long-term data on the effectiveness of primary banded one-anastomosis gastric bypass (OAGB) are lacking.

**Methods:**

A total of 210 patients will be included in this prospective, non-blinded, single-center randomized controlled trial. The primary endpoint is the difference in total weight loss percentage (%TWL) 5 years post-surgery. Secondary outcomes include excess weight loss percentage (%EWL), changes in obesity complications, quality of life, and adverse events related to the surgical procedures. The study population will consist of patients eligible for primary OAGB aged 18 years and older.

**Conclusions:**

The RiMini trial aims to investigate whether there is a significant difference in long-term weight reduction expressed as %TWL in patients undergoing an OAGB with or without the addition of a silicone ring 5 years after surgery.

**Trial Registration:**

This study is registered at Clinicaltrials.gov (NCT05472922) on the 25th of July, 2022.

**Graphical Abstract:**

[figure not shown]

## Introduction

Overweight and obesity have reached epidemic proportions worldwide, contributing to an array of chronic health conditions significantly impacting overall public health. In the Netherlands, this global challenge is also evident, with approximately 50% of adults being overweight, 16% suffering from obesity, and 4% classified as severely obese [1]. Obesity is associated with an elevated risk of complications such as diabetes mellitus, hypertension, obstructive sleep apnea syndrome (OSAS), osteoarthritis, gastroesophageal reflux disease (GERD), and dyslipidemia. Obesity reduces life expectancy by 8 to 10 years, similar to smoking, and is a major avoidable cause of cancer, responsible for one in seven cancer deaths in men and one in five in women [2, 3]. Given the severe health consequences of obesity, metabolic bariatric surgery (MBS) has emerged as a crucial treatment option and is considered the most optimal treatment for significant weight loss and reduction or remission of obesity complications [4].

However, recurrent weight gain after initial weight loss remains a persistent challenge. Defining the prevalence of significant recurrent weight gain is complicated due to various factors such as patient characteristics, anatomic variations, surgical techniques, follow-up periods, and, most importantly, the lack of a standardized definition for recurrent weight gain [5–7]. Approximately 50% of post-bariatric surgery patients experience recurrent weight gain of at least 5% of their initial body weight within the first 2 years after surgery [8]. Estimates for more significant recurrent weight gain range from 20 to 30% [9], although some studies with small sample sizes have reported even higher rates [6].

Recently, the International Federation for the Surgery of Obesity and Metabolic Disorders (IFSO) updated their statement on the effectiveness of the OAGB as a weight loss procedure [10]. They stated that the OAGB is at least equivalent to RYGB and potentially superior to sleeve gastrectomy (SG) and gastric banding (GB). OAGB has also been promoted by some as a technically easier and safer alternative to the RYGB [11].

As with other bariatric procedures, patients can struggle with recurrent weight gain after initially optimal OAGB [12]. As mentioned before, addressing weight gain is a complex and multifaceted challenge. In some cases, revisional MBS is considered an option, but some of these revisional procedures are associated with a considerably high risk of complications and often yield unsatisfactory outcomes [9]. The most commonly known revisional procedures are conversion from the gastric band or sleeve to a gastric bypass, limb lengthening of a gastric bypass, or pouch revision including revision of the gastro-jejunal anastomosis. A new alternative to the abovementioned revisional procedures involves longitudinal reduction of the pouch (or sleeve) and placement of a non-adjustable silicone ring around the gastric pouch. This technique may also lead to more significant weight loss and a reduced risk of long-term recurrent weight gain [13, 14]. Given the challenges posed by recurrent weight gain, it seems more reasonable to pursue all possible ways of reducing the risk of recurrent weight gain at the time of the primary procedure.

While studies have suggested the effectiveness of silicone rings in combination with primary RYGB, there is a lack of data on their use with primary OAGB [14]. Although the OAGB and RYGB share similar mechanisms of action, they differ in certain anatomical aspects such as pouch dimensions. Traditionally, the RYGB with a small pouch is considered to have a more restrictive nature, while the OAGB, with its longer and narrower pouch, is thought to be more hypo-absorptive. However, recent studies have introduced successful modifications to the RYGB, such as a longer pouch and an extended biliopancreatic limb, which resemble some of the characteristics of the OAGB [15]. Conversely, the addition of a silicone ring to the OAGB may enhance restriction, addressing a potential limitation in the original procedure. To date, no randomized studies have provided (long-term) data on the effectiveness of primary banded OAGB.

The RiMini trial aims to investigate whether incorporating a silicone ring during primary OAGB improves weight reduction, measured as %TWL 5 years after surgery, compared to classic OAGB. Secondary endpoints include changes in obesity complications, quality of life, and adverse events related to surgical procedures.

## Methods

### Study Design and Patient Selection

This study is a single-center, non-blinded, prospective randomized controlled trial. The intervention group consists of patients undergoing standard OAGB with the addition of a MiniMizer silicone Ring (Bariatric Solutions GMBH, CH-8260 Stein am Rhein), placed 2 to 4 cm below the esophagogastric junction (see the “Surgical Techniques” section). The control group consists of patients undergoing standard OAGB without the addition of the silicone ring. All procedures will be performed by one of five bariatric surgeons. Of these, two surgeons will exclusively perform standard OAGB in the control group, while the other three surgeons will conduct both the intervention and standard procedures.

Patients meeting the general (inter)national criteria for MBS [4] are potentially eligible for participating in this study. Exclusion criteria are shown in Table 1. Patients are informed about the study during their preoperative screening. Participation is voluntary, and patients are offered a 2-week period to consider their decision before signing the informed consent form.

**Table 1 Tab1:** Exclusion criteria

Previous MBS
Insufficient proficiency in the Dutch language
Genetic conditions affecting compliance with medical advice
Chronic inflammatory bowel diseases
Renal dysfunction (eGFR < 30) or liver dysfunction (ASAT/ALAT twice the normal values)
Pregnancy before or during the study
Clinically severe therapy-resistant GERD
Silicone allergy

After providing informed consent, patients are randomly assigned to one of the two groups using a computer-generated randomization sequence to ensure balanced allocation.

All patients will receive standard multidisciplinary pre- and postoperative care, in accordance with the local standards of care. This includes preoperative blood tests and the “Modifast Intensive®” diet for 2 weeks, providing 850 kcal/day to reduce liver volume, promote weight loss, and improve surgical conditions and recovery [16]. Postoperative care is provided for 4 months, followed by annual evaluations for up to 5 years, including blood tests and assessment of obesity complications. In this study, patients will also complete standardized questionnaires in addition to the standard care (see the “Quality of Life” section).

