### Statistical Analysis

IBM’s Statistical Package for the Social Sciences (SPSS) is utilized for the statistical analyses of the obtained data. Histograms (visual inspection) are used to ascertain whether variables are normally distributed. A significance level (alpha) of 0.05 is applied to all analyses unless stated otherwise. Differences in baseline characteristics of the study groups are tested using the independent *t*-test (for continuous, normally distributed data), the Mann–Whitney test (for non-normally distributed or ordinal data), or the chi-square test (for categorical data).

Assumptions for linear regression will be checked for all outcomes, including normality of residuals and homogeneity of variances. Where necessary, transformations (e.g., log transformation) were applied to meet model assumptions.

Difference between groups in %TWL, %EWL, and GERD-HRQoL at 5 years postoperative will be assessed using the independent *t*-test or Mann–Whitney test (for normally or non-normally distributed data, respectively). Baseline characteristics related to both the type of surgery and outcome variables (with *p*-value < 0.15) will be considered confounders in the analyses. If one or more confounders are identified, linear regression models will be used to assess differences between groups in %TWL, %EWL, and GERD-HRQoL at 5 years postoperative, each adjusted for relevant confounders.

The difference between groups in the reduction of obesity complications at 5 years postoperative will be tested using chi-square tests for each comorbidity. Holm-Bonferroni correction will be used to correct for multiple testing.

Chi-square tests will be used for the difference between groups in change of scores of the questionnaires, early and late dumping, and reflux. Additionally, a linear mixed model analysis will test the difference in change in the subscales of the SF-36 and OBESI-Q over time between groups.

The difference in the total number of complications between groups will be tested with independent *t*-tests or Mann–Whitney tests (for normally or non-normally distributed data, respectively).

Missing data will be reported if known. A sensitivity analysis will be performed for the primary outcome: analysis of the data “as-is” (without imputation) will be compared with the results of the analysis where missing data is imputed.

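### Two of the five surgeons operate only on controls and the planned comparison has no surgeon term, so the ring effect is partly confounded with the operator

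*Protocol article*

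**What the plan says.** Under Study Design and Patient Selection, the protocol article says "All procedures will be performed by one of five bariatric surgeons", and that "two surgeons will exclusively perform standard OAGB in the control group, while the other three surgeons will conduct both" procedures. Every ring patient is thus treated by one of three surgeons, and control patients by any of five. In the same section, "patients are randomly assigned to one of the two groups using a computer-generated randomization sequence to ensure balanced allocation"; stratification by surgeon is not mentioned.

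Under Statistical Analysis, "Difference between groups in %TWL, %EWL, and GERD-HRQoL at 5 years postoperative will be assessed using the independent" t-test or the Mann–Whitney test. The candidates for adjustment are "Baseline characteristics related to both the type of surgery and outcome variables", screened at p < 0.15. If any pass, linear regression models are fitted for %TWL, %EWL and GERD-HRQoL, "each adjusted for relevant confounders". The total number of complications is compared with a t-test or Mann–Whitney test, and no adjusted model is named for it. Surgeon appears in none of the randomisation, sample size or analysis text.

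Under Surgical Techniques, the operation is standardised for all study patients: the calibration tube, the limb length by BMI, the stapled anastomosis, the closing suture and the leak test.

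**The concern.** Randomisation balances what is fixed before allocation. The operator is not fixed before allocation here: a patient allocated to the ring cannot be treated by the two control-only surgeons, and a patient allocated to control can. The operator mix is therefore a consequence of the arm, and a larger sample does not even it out.

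The operator can plausibly affect weight loss, through the construction of the pouch and anastomosis. It can also affect complications; the article's list includes bleeding, leaks and abscesses. If the two control-only surgeons' patients do better or worse than the others' under the same operation, part of that difference is counted as a ring effect. It can create an apparent benefit or hide a true one.

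The confounder rule is unlikely to catch this. It is worded for baseline characteristics, which a reader would take to mean the patient's, and it admits a variable only if a significance screen happens to select it. For complications the article names no adjusted model at all.

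**Working it through.** **Inputs from the document** (Sample Size Calculation): target difference 5 %TWL points (32 against 27), SD 10, two-sided alpha 0.05, power 80%, 63 analysed per arm, 40% loss to follow-up, 105 enrolled per arm.

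**Reproducing the plan's figure.** Normal approximation: n = 2 × (1.96 + 0.842)² × 10² / 5² = 62.8, so 63 per arm. 63 / 0.60 = 105 per arm. Both reproduce. The standard error of the planned difference is 10 × √(2/63) = 1.78 points.

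**Assumptions, because the document gives no values.** Let s be the share of controls treated by the two control-only surgeons. Let d be the difference in mean 5-year %TWL between those surgeons' patients and the other three surgeons' patients under the same operation.
- Controls spread evenly over five surgeons: s = 2/5 = 40% (42 of 105).
- Equal total caseloads: 210 / 5 = 42 each, so the two surgeons treat 84 of 105 controls, s = 80%.

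**Fixed surgeon difference.** Bias = s × d. Type I error = Φ(bias/SE − 1.96) + Φ(−bias/SE − 1.96).

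| d (points) | Bias, s = 40% | Type I error | Bias, s = 80% | Type I error |
|---|---|---|---|---|
| 0 | 0 | 5.0% | 0 | 5.0% |
| 1 | 0.4 | 5.6% | 0.8 | 7.3% |
| 2 | 0.8 | 7.3% | 1.6 | 14.6% |

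A bias of 0.8 to 1.6 is 16% to 32% of the 5-point target. If a bias of that size runs against the ring, power is Φ((5 − bias)/1.78 − 1.96), which is 65% at 0.8 and 48% at 1.6, instead of 80%.

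**Random surgeon effects.** Suppose surgeons vary with variance τ² = ICC × 100, and cases are spread evenly within each surgeon group. In the arm difference each dual-procedure surgeon then has weight s/3 and each control-only surgeon −s/2. The added variance is τ² × (3 × s²/9 + 2 × s²/4) = τ² × s² × 5/6. The true variance is (100 − τ²) × 2/63 plus this term; the t-test assumes about 200/63 = 3.17.

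| s | ICC | True variance | Ratio of true to assumed SE | Type I error |
|---|---|---|---|---|
| 40% | 0.02 | 3.38 | 1.03 | about 6% |
| 40% | 0.05 | 3.68 | 1.08 | about 7% |
| 80% | 0.02 | 4.18 | 1.15 | about 9% |
| 80% | 0.05 | 5.68 | 1.34 | about 14% |

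**Precision of a surgeon-adjusted analysis.** With surgeon as a fixed effect, only the three dual-procedure surgeons' controls inform the ring contrast. Assuming the same arm split at each of them, SE = 10 × √(1/63 + 1/(63(1 − s))).
- s = 40%: 37.8 controls, SE 2.06, power for 5 points 67%.
- s = 80%: 12.6 controls, SE 3.09, power 36%.

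Power is from the noncentral t distribution with 126 − 6 = 120 degrees of freedom.

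**The case against.** **The effect may be small or absent.** The document gives no caseload, surgeon difference or ICC. The trial is single-centre, care before and after surgery is common to both arms, and the technique is standardised at the very steps through which an operator would act. This stands as a limit on the likely size. It does not remove the operator: calibration is described as loose, and a written technique does not make five surgeons' results equal.

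**The trial can separate ring from operator.** A reader might infer that the two are inseparable. The document does not support that: three surgeons work in both arms, so a within-surgeon contrast exists. What is missing is a planned analysis that uses it.

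**An analysis plan not shown could add a surgeon term.** It could, and on a generous reading surgeon might even enter the confounder screen. But the article fixes both the comparison and the adjustment rule without naming surgeon, and no analysis plan can undo the allocation of surgeons.

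**The remedy has weaknesses.** Using only the dual-procedure surgeons' controls selects on something that happens after randomisation. If controls go to surgeons by case difficulty, that subset is no longer a randomised comparator, and surgeon terms do not cure this. At 67% or 36% power, a rule that required the adjusted result to be significant would often reject a true effect. Both points stand and shape the fix.

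**Conclusion.** The concern holds in a limited form. Operator mix differs by arm by design, and the analysis as written neither adjusts for surgeon nor uses the within-surgeon information that the three dual-procedure surgeons provide.

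The size cannot be derived from the document. It is nil if surgeons' results do not differ. It is modest if control cases are spread evenly over the five surgeons. It becomes material if most controls go to the two control-only surgeons and those surgeons' results differ by about 2 points. The upper figures should therefore not be read as an estimate of the trial's actual error rate; they depend on an assumed 80% share.

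This should be fixed, since the supportive analysis is cheap and loses credibility if it is specified after results are known. It does not by itself invalidate the trial.

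**What to change.** 1. Before 5-year data are seen, pre-specify a supportive analysis of %TWL and of complications with surgeon as a fixed effect, so that the ring contrast comes from the three dual-procedure surgeons. With only five surgeons, a random surgeon effect would be weakly estimated.
2. Report its estimate and 95% confidence interval beside the primary result, with caseload by surgeon and arm. Judge consistency by the direction and size of the estimate, not by significance.
3. State how control patients are assigned to surgeons, and adjust this analysis for baseline weight or BMI, because the contrast rests on controls selected after randomisation.
4. If patients remain to be operated on and scheduling allows, assign the surgeon from among the three dual-procedure surgeons before, or independently of, allocation, and stratify allocation by surgeon. If those three did all cases in both arms, surgeon terms would cost almost no power (79.5% at 63 per arm). The document does not give recruitment status, so this step is secondary.

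**Cost.** Steps 1 to 3 need one added analysis and the surgeon's identity for each operation. Precision is lower: SE about 2.1 to 3.1 points against 1.8, and power for 5 points about 67% or 36%. To make it the primary analysis at 80% power would need about 84 analysed (140 enrolled) per arm at s = 40%, or 189 (315) at s = 80%. It should therefore support the primary result and not replace it. Step 4 costs theatre flexibility.

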### Sample Size Calculation

In order to obtain mid-term results, a 5-year follow-up period has been selected, consistent with standard practices in Dutch metabolic bariatric surgery. A total of 63 patients per group is necessary to detect a 5% difference %TWL between groups 5 years post-surgery. This calculation is performed using PASS software, with parameters set at power = 80%, alpha = 0.05, standard deviation = 10%, and average %TWL of group 1 vs. group 2 being 32 vs. 27, assuming a two-sided independent *t*-test.

Jense et al. observed a loss-to-follow-up (LtfU) ranging from 21 to 58% three to five years postoperatively [21]. To have sufficient power for the 5-year analysis, this study takes into account a LtFU of 40%, assuming that actively contacting patients will reduce LtFU at 5 years postoperatively. Based on a required sample of 63 individuals per group and an expected LtFU of 40%, we aim to include 210 patients for this study, 105 per group.

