## Outcome Measurement

All outcomes are measured at 4 months and annually up to 5 years postoperatively.

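### The pregnancy exclusion extends over five years of follow-up, so applying it as written would exclude women after randomisation and surgery

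*Protocol article*

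**What the plan says.** In the protocol article, Study Design and Patient Selection states that "Exclusion criteria are shown in Table 1", and one entry in that table is "Pregnancy before or during the study". It is the only mention of pregnancy in the article.

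The same section fixes when allocation happens: "After providing informed consent, patients are randomly assigned to one of the two groups using a computer-generated randomization sequence". It also describes the trial as non-blinded. Outcome Measurement sets the length of follow-up: "All outcomes are measured at 4 months and annually up to 5 years postoperatively". The abstract describes the population without limiting it by sex or childbearing potential ("The study population will consist of patients eligible for primary OAGB aged 18 years and older") and gives the primary endpoint: "The primary endpoint is the difference in total weight loss percentage (%TWL) 5 years post-surgery".

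Two other sections bear on the point. Secondary Outcomes counts every complication up to 5 years, whether or not it may be linked to the ring. Statistical Analysis plans, for the primary outcome, a comparison of the unimputed result with an imputed one as a sensitivity analysis. It does not mention pregnancy.

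**The concern.** An exclusion criterion is normally something that can be checked before a patient is randomised. Pregnancy in the years after the operation cannot be. The second half of the criterion can therefore act only on women who already have an assigned arm and have mostly had their surgery.

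If such women were taken out, the groups compared at 5 years would no longer be the groups formed by randomisation. They would be selected on an event that happened after allocation, in a trial where patients and staff know the arm. If the ring affected who conceives, or which women do, the %TWL difference would be biased. Any complications in these women, ring-related ones included, could also be lost from the safety comparison, although the article says elsewhere that all complications count.

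A lesser matter is that pregnancy before the study is given no time point, so the text does not say whether it means pregnancy at screening, within some recent period, or at any time.

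**Working it through.** **Setting the passages side by side**

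1. Table 1 makes pregnancy during the study an exclusion criterion.
2. Randomisation follows consent and decides which operation is done, so it precedes surgery.
3. Outcomes are collected from 4 months to 5 years after surgery.
4. From 1 to 3, the period in which the criterion could be met runs from randomisation through the 5 postoperative years. Excluding a woman on this ground means excluding her after randomisation and, except in the short interval before the operation, after surgery.
5. Secondary Outcomes counts all complications to 5 years. A woman excluded under Table 1 would be left out of a count that this section describes as complete. The two passages can be reconciled only if exclusion does not remove her from the analysis, and the article does not say that.
6. The imputed sensitivity analysis deals with missing weights of patients who belong to the analysis. It does not say whether a woman meeting an exclusion criterion still belongs to it.

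**The planned size**

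Inputs from Sample Size Calculation: difference of 5 points ("average %TWL of group 1 vs. group 2 being 32 vs. 27"), SD 10, two-sided alpha 0.05, power 80%, loss to follow-up 40%.

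- Normal approximation: n = 2 × (1.960 + 0.842)² × (10/5)² = 62.8, so 63 per group, as stated. The exact t-test gives 63.8, so 64, a trivial difference.
- Inflation: 63/0.60 = 105 per group, 210 in total. This agrees with "we aim to include 210 patients for this study, 105 per group".
- In reverse, 105 × 0.60 = 63. The 40% is justified by loss to follow-up alone and leaves no reserve for another source of removal.

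**Illustration only**

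The article gives no pregnancy rate. The table assumes that a share p of the patients otherwise evaluable at 5 years is removed for pregnancy, wholly on top of the 40%. Evaluable n = 63 × (1 − p); total needed = 2 × 63/[0.60 × (1 − p)], each group rounded up.

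| p (assumed) | Evaluable per group | Power, normal approx. | Power, exact t | Total to keep 63 per group |
|---|---|---|---|---|
| 0% | 63.0 | 80.1% | 79.5% | 210 |
| 2% | 61.7 | 79.3% | 78.7% | 216 |
| 5% | 59.9 | 78.1% | 77.4% | 222 |
| 10% | 56.7 | 75.9% | 75.2% | 234 |
| 15% | 53.6 | 73.5% | 72.7% | 248 |

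The table shows how sensitive the design would be. It is not an estimate for this trial.

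**The case against.** The strongest defence is that the article never says a woman who becomes pregnant is withdrawn, stops follow-up or leaves the analysis. The phrase stands in an eligibility table. Analysis sets and the handling of later events are commonly left to a full protocol or SAP, which is not shown here. This stands in part: actual removal is an inference, so the point has to be conditional. It does not dispose of the point, because the problem is a stated criterion with an unsuitable time span. A later document that keeps these women would have to depart from Table 1.

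Second, the complications rule points towards inclusion. That stands too. A reader might infer that the safety comparison is already broken, but the text supports only a tension between two passages.

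Third, both arms receive OAGB. Bias between arms would need the ring's added effect to change conception or the kind of women who conceive. The article contains nothing on that, nor on any link between weight loss and conception. Bias is therefore possible but not shown.

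Fourth, the power figures rest on assumed rates in a population with no sex or upper age limit, and they assume no overlap with loss to follow-up. The 40% is itself a planning value chosen within a cited range of 21 to 58%. This stands in full.

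Finally, a literal reader might conclude that every woman who has ever been pregnant is barred. That reading is strained. Current or recent pregnancy is probably meant, and nothing suggests that mothers are kept out.

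**Conclusion.** The point holds in conditional form. The criterion covers 5 years after randomisation and surgery, and applying it as written would be a post-randomisation exclusion in an open-label trial. This could bias the 5-year %TWL comparison, and it is in tension with the complete count of complications. The rule is badly fixed in stated text; it is not detail left out of a condensed article.

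The article does not establish that women are in fact dropped, that the %TWL or complication comparison is biased, or that power falls by any given amount. Under assumed removals of 2% to 15% beyond the 40%, power by the normal approximation would lie between about 79% and 73% instead of 80%. No rate in the article says where in that range the trial would fall, or whether it would fall there at all. The planned 210 is arithmetically sound and needs no change if these women stay in the analysis. The undefined time point for earlier pregnancy is a minor wording matter. The point should be corrected, with moderate confidence about its practical effect.

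**What to change.** - **Table 1:** restrict the criterion to pregnancy at inclusion. This also settles the missing time point for pregnancy before the study.
- **Statistical Analysis:** state that randomised women who later become pregnant stay in follow-up and are analysed in their assigned arm for all outcomes, including complications.
- **Weights:** treat only a weight recorded during pregnancy as missing for that visit. Handle it like any other missing weight: absent from the unimputed analysis and imputed in the sensitivity analysis already planned for the primary outcome. No new missing-data method is needed.

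The cost is an amendment to one table entry and an added line of analysis text, with no extra patients or procedures. The small downside is that a few 5-year weights will be set to missing. For the primary endpoint this affects only women who are pregnant at the 5-year visit, whereas the present wording reaches anyone pregnant at any time in the 5 years.
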